#### Sample size

A sample size of 480 couples, 120 per each of the four study arms, was chosen to ensure sufficient statistical power to detect meaningful differences in our primary outcomes of couple-level ART/PrEP initiation and adherence between intervention and control groups. These power calculations assume 80% power, and an intraclass correlation coefficient (ICC) of 0.05 (based on the team’s previous R01 study with couples in Cape Town) [22], with an estimated follow-up of 95% at 3-month follow-up and 90% at 6-month follow-up. On average, a sample size of 97 community members in each of the 24 catchment areas was calculated to detect a 10% difference between control and intervention conditions on measures of stigma reduction. Using a two-sided chi-square test of proportions with a significance level of 0.05 and nested design model with additivity on the primary intervention effect (stigma awareness community workshop as compared with no community workshop) and secondary intervention effect (CHC+ as compared with HTS), our sample size was selected to ensure power for contrasts based on the presence of an interaction between the community-based stigma awareness workshop and the CHC+. For a hypothesis related to ART/PrEP initiation among couples in the CHC+ arm as compared with couples in the HTS arm, we will be able to detect a minimal effect size of 0.23. The minimal effect size of the CHC+ intervention on ART/PrEP adherence by couples in the CHC+ arm at 6 months is estimated to be 0.34 compared with couples in clinics in the HTS arm. For the evaluation of the efficacy of the stigma awareness workshop plus the CHC+ as compared with no stigma awareness workshop plus HTS (control), the minimal effect size related to ART/PrEP initiation is estimated to be 0.45. For examination of the intervention components’ effects (stigma awareness workshop and the CHC+) on ART/PrEP adherence), the minimal effect size is estimated to be between 0.26 and 0.6 for retention at 3-month and 6-month follow-up.

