#### Screening: Couples

During the initial contact, individuals will be approached, and verbal consent will be obtained to screen for eligibility. To ensure privacy and confidentiality, the screening process will be conducted individually, with female staff screening the female partner and male staff screening the male partner. In cases where both partners are not present during the initial outreach, screening appointments will be scheduled to facilitate simultaneous screening and determine preliminary eligibility. For the screening process, project staff will use a quick screener form, which allows for efficient and standardized assessment of eligibility criteria. To maintain the integrity of the screening process, staff members will compare answers away from the screened couple to determine initial eligibility. Individuals’ responses are not disclosed to their partner. To respect privacy, couples who are found to be ineligible are not be provided with explanations for their ineligibility, but they will be respectfully informed that they do not meet the criteria for participation. After this initial eligibility screening, biological verification for eligibility is scheduled and conducted at the project site. Both partners are tested for HIV and the female partner is tested for pregnancy. If either partner has an indeterminant HIV test or the female partner has a positive pregnancy test, they are both not eligible.

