#### Overall study measures

We aim to assess the impact of the stigma awareness workshop on the knowledge, attitudes, and behaviors of the community toward young women and men who are seeking or need health services. Community-level outcomes will be evaluated through repeated measures on their beliefs about people who use alcohol or other drugs, their knowledge about ART and PrEP, their attitudes, beliefs, and behaviors toward people living with HIV, challenges or support from the community to take HIV prevention, and where to go for needed health services and information.

At the couple level, our primary outcomes will include the initiation of ART/PrEP and the documentation of HIV status. We will measure ART/PrEP adherence, as well as PrEP concentration via medical records and dried blood spot (DBS) samples during follow-up appointments. Adherence will also be assessed through self-reported past 30-day use, refills, and the duration of ART or PrEP usage, documented medical records, and DBS. To evaluate substance use, we will conduct baseline and follow-up assessments using rapid urine-based drug screening. This method will detect metabolites of commonly used drugs, providing insight into recent AOD use. Furthermore, we will examine secondary couples-level outcomes, such as self-reports on the frequency of AOD use; experiences of GBV; sexual risk behaviors, including condomless sex; AOD use before sexual encounters; engagement in concurrent partnerships; involvement in sex trade; contraceptive use; and perceptions of HIV risk. We will also assess attitudes toward traditional gender roles, empowerment, assertiveness, and communication between partners regarding testing, status, or sexual relationships. Participants will be asked to self-report experiences of stigma in their communities. To measure these outcomes, we will use a revised risk behavioral assessment (RRBA) [39] that also includes ART/PrEP partner support, treatment readiness, social impact of ART/PrEP use, and health service access and utilization (see **Table 3**).

**Table 3 pone.0305056.t003:** Outcome measures for couples and communities.

Outcome	Measures	Time Points Revised
**Aim 2: Stigma awareness and education on community members’ attitudes and behaviors toward young women and men who use AODs and other people seeking HIV services (testing/ART/PrEP) and other health services.**		

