Increased communication between partners regarding testing, HIV, and STI/STD status; other partners; sexual negotiation; and condom use.	**Self-report:** Communication with partner about testing, HIV and STI/STD status, other partners, sexual negotiation and condom use as measured by the PRBA+.	Baseline, 3 months, and 6 months FU
**Aim 3: The Couples Health CoOp Plus proposes to increase both partners’ PrEP/ART initiation and adherence. fgAim 4: Examine the interaction of the stigma awareness workshops and Couples Health CoOp Plus intervention on increased PrEP and ART initiation, retention, and adherence for both partners.**		
FGEvidence of ART or PrEP initiation.	**Medical Record Review:** ART/PrEP initiation and HIV status as documented by medical record.	6 months FU
Increased biological evidence of ART or PrEP adherence.	**Biological:** ART adherence will be measured using viral load or cluster of differentiation 4 (CD4) count measures recorded in the participant’s medical record. Threshold for adherence will be cluster of differentiation 4 (CD4) count (more than 200) and HIV viral load (less than 50 copies per ml). Tenofovir Diphosphate (TFV-DP) and FTC Triphosphate (FTC-TP) concentrations in dried blood spots (DBS) with drug concentrations of greater than 700 femtomoles (fmol)/liters(L) will be considered adherent to PrEP.	6 months FU
Increased reporting ART or PrEP adherence.	**Self-report:** Past 30-day use, missed doses, time in weeks, and patterns of use of ART or PrEP as measured by the RRBA/PRBA+.	3 months, and 6 months FU
Increased evidence ART or PrEP adherence; Increased persistence and reduced discontinuation.	**Medical Record Review:** Refills, number of months on ART/PrEP since initiation, and follow-up visit attendance as recorded in clinic medical records.	6 months FU
**Note:** AOD, alcohol and other drugs; ART, antiretroviral therapy; ASSIST, Alcohol, Smoking and Substance Involvement Screening Test; GIS, Gender Ideology Scale; PRBA+, Pretoria Risk Behavior Assessment; PrEP, pre-exposure prophylaxis; RRBA, Revised Risk Behavior Assessment; SRH, sexual and reproductive health; STI/STD, sexually transmitted infection/disease.		

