### Statistical analysis plan and hypotheses

We will examine the distribution, frequency, and missing values in each variable using frequency tables for categorical variables and univariate distributions for continuous variables. We will compare data across the arms to examine the balance of baseline demographic and clinic characteristics using chi-square tests and t-tests or their nonparametric alternatives, as appropriate. Next, we will examine the association between demographics, clinic characteristics, primary outcomes, and any important mediators and moderators to determine which variables will be entered in the generalized linear models (GLM). We will use a GLM with generalized estimating equations (GEE) to test the relative efficacy of the interventions on the primary outcomes. GEE allows one to adjust for clustering and accommodates multiple types of outcomes (dichotomous, continuous, ordinal) and dyadic data analysis. We will use the couple as the unit of analysis for ART/PrEP initiation and adherence. First, we will fit a logit model that regresses the dependent variable on the membership in the arms and visit, and an interaction between visit and arm. Second, if descriptive analysis suggests there are significant differences in demographics or characteristics of clinics across the arms, those variables will be added into the model as covariates. We will test ART/PrEP initiation and adherence across two arms at a time by estimating contrasts at each time point to test both the hypotheses that the CHC+ increases ART/PrEP initiation and adherence. We will use an identical process to estimate the impact of the interventions on AOD use, GBV, sexual risk-taking, communication, and gender norms. The distribution in the GLM will be modified to be multinomial for ordinal outcomes, binary for dichotomous outcomes, and continuous or Poisson for continuous or count outcomes, respectively. The unit of analysis for outcomes (e.g., condomless sex) will be at the couple level and/or individual level, when appropriate, which the study team has done in previous couples-based analyses [15]. Analyses will be performed for the 3-month and 6-month follow-up time periods to determine if there are differential effects over time on ART/PrEP initiation and adherence, and at the 6-month time period for secondary outcomes.

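### Couple-level initiation and adherence each pool ART with PrEP, and baseline HIV status is neither a prespecified covariate nor the basis of stated component analyses, which costs precision and interpretability

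*Protocol article*

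**What the plan says.** The Sample size section powers the trial for "our primary outcomes of couple-level ART/PrEP initiation and adherence between intervention and control groups". The Overall study measures section words it somewhat differently but keeps the combined term: "our primary outcomes will include the initiation of ART/PrEP and the documentation of HIV status". The Statistical analysis plan section then states: "We will use the couple as the unit of analysis for ART/PrEP initiation and adherence".

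The model is described in two steps. Its base terms are study group, visit and the interaction of the two: "we will fit a logit model that regresses the dependent variable on the membership in the arms and visit, and an interaction between visit and" (the quote stops one word before the sentence ends). Further covariates enter only on a condition, which the article words as: "if descriptive analysis suggests there are significant differences in demographics or characteristics of clinics across the arms, those variables will be added into the model". An earlier sentence in that section allows unnamed mediators and moderators to be examined for entry. Baseline HIV status is named in none of these places.

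Status is available before enrolment. Under Screening: Couples, "Both partners are tested for HIV and the female partner is tested for pregnancy", and as regards HIV only an indeterminate result excludes, so partners of either status can enter. The Randomization section gives population group as the only stratification factor, with two communities per arm in each of three strata, hence 6 per arm.

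Table 3 measures adherence differently for the two treatments. For ART, "ART adherence will be measured using viral load or cluster of differentiation 4 (CD4) count measures recorded in the participant’s medical record". For PrEP, the measure is drug concentration in dried blood spots.

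**The concern.** For an HIV-positive partner the relevant event is starting ART; for an HIV-negative partner it is starting PrEP. One is treatment of an infection and the other is prevention in a person who is well, so uptake may differ a great deal, and adherence is judged by different instruments. Baseline HIV status is therefore likely to be strongly prognostic for both pooled outcomes.

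Two things are at stake. The first is precision: a known prognostic variable is left out of the stated model unless an open-ended, data-dependent step happens to admit it, so chance differences in HIV mix stay in the estimate. The second is interpretation: Aim 4 speaks of PrEP and ART initiation, retention and adherence, but a pooled difference cannot be traced to either treatment.

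**Working it through.** The article gives no initiation rates and no HIV prevalence, so every size below rests on stated assumptions.

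**Inputs from the article.** 20 couples per community; 6 communities (120 couples) per arm; 12 against 12 communities (240 against 240 couples) if CHC+ is compared with HTS across workshop conditions; ICC 0.05, two-sided 0.05, 80% power.

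**Assumptions.** Share q of couples with an HIV-positive partner, 0.2 to 0.4; community ICC of HIV status, 0.02 to 0.10; gap in initiation between couples with and without an HIV-positive partner, 20 to 50 points.

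**1. Chance imbalance in HIV mix.** SD of the between-side difference = √(2q(1−q)·DE/N), with DE = 1 + 19 × ICC and N couples per side.

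- Low end (q = 0.2, ICC 0.02, DE = 1.38): 12 v 12, √(2 × 0.16 × 1.38/240) = 0.043; 6 v 6, 0.061.
- High end (q = 0.4, ICC 0.10, DE = 2.90): 12 v 12, √(2 × 0.24 × 2.90/240) = 0.076; 6 v 6, 0.108.

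Multiplying by 1.96 gives 95% limits of 8 to 15 points (12 v 12) and 12 to 21 points (6 v 6).

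**2. Resulting shift in pooled initiation with no intervention effect.** Imbalance × gap:

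| Comparison | Low end | High end |
|---|---|---|
| 12 v 12 | 0.084 × 0.20 = 0.017 | 0.149 × 0.50 = 0.075 |
| 6 v 6 | 0.119 × 0.20 = 0.024 | 0.211 × 0.50 = 0.106 |

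That is about 2 to 7 and 2 to 11 points. These are 95% limits; a one-SD shift is about half as large. The formula ignores any balance in HIV mix that stratification by population group may bring.

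**3. Noise or bias?** In 20,000 simulated trials with no intervention effect and HIV mix varying at random by community, a cluster-level t-test rejected in 4.9%. The Monte Carlo standard error is √(0.05 × 0.95/20,000) = 0.15 points, so this agrees with the nominal 5%. Unadjusted mix widens the between-community variance, and a valid cluster analysis counts that variance.

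**4. What a pooled gain can hide.** Treat the pooled gain as q × ART gain + (1 − q) × PrEP gain, with q = 0.3. The same 9 points arise from:

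- ART +30, PrEP 0: 0.3 × 30 = 9
- ART 0, PrEP +12.9: 0.7 × 12.9 = 9
- both +9: 2.7 + 6.3 = 9
- ART −10, PrEP +17.1: −3 + 12 = 9

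**5. Precision of a split.** Standardised minimal effect = 2.80 × √(2·DE/n), with DE = 1 + (m − 1) × 0.05, m couples per community, and no attrition. Pooled, 240 per side and DE = 1.95: 0.36. The article's 0.23 for initiation is not reproduced by this formula; its effect-size scale and the level of its ICC are not stated, and nothing here depends on it. Split by whether the couple has an HIV-positive partner:

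| q | With HIV-positive partner | Without |
|---|---|---|
| 0.2 | 0.61 (n = 48) | 0.38 (n = 192) |
| 0.3 | 0.52 (n = 72) | 0.39 (n = 168) |
| 0.4 | 0.47 (n = 96) | 0.41 (n = 144) |

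The split is by couple, so it is only a guide to partner-level analyses.

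**The case against.** The strongest reply is that randomisation already deals with HIV mix: communities were allocated at random within strata, and chance differences are part of the sampling variance. That stands. A reader might infer that unadjusted HIV mix confounds the arm comparison; step 3 shows it does not inflate the error rate of a valid cluster analysis. Systematic bias would need recruitment of couples to depend on arm. Couples are recruited into communities already assigned, so this cannot be excluded, but the article gives no evidence of it.

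Pooling is also a coherent choice. The intervention is described as status-neutral, and an outcome of each partner being on the option suited to their status fits that. A reader might take Aim 3 to promise an effect on both drugs; there the word refers to both partners. Aim 4's wording does name the two treatments. Nor is everything folded into one endpoint: initiation and adherence are separate outcomes with separate effect sizes (0.23 and 0.34), and Table 3 records ART and PrEP adherence separately, so the components can be reported.

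Finally, the mediator and moderator step could admit HIV status, and a fuller analysis plan may exist. It would therefore be too strong to say that adjustment is ruled out. What remains is that the article does state the model and its covariate rule, and that rule names only demographics and clinic characteristics and triggers on significance. With 6 communities per arm, such tests can miss imbalances that matter.

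Baseline status also does not fix the event absolutely: baseline-negative participants are retested, and one who seroconverts can start ART.

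**Conclusion.** The point holds as one of precision and interpretability. Both couple-level outcomes pool ART with PrEP, and a variable that is known at entry and very probably strongly prognostic is not a prespecified term or a stratum. Under the assumed rates, chance mix can move a realised initiation difference by up to about 2 to 11 points (6 v 6) or 2 to 7 points (12 v 12) at the 95% limit. The sizes depend on those assumptions, and the 4.9% error rate comes from a cluster-level t-test, not from the planned GEE.

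The documents do not support calling this systematic confounding. The interpretive limit does not depend on chance: even a well-estimated pooled effect cannot say whether ART, PrEP or both improved, and could in principle conceal opposite movements. The change is worth making but does not threaten the trial's validity.

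**What to change.** In the Statistical analysis plan section:

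- Keep the pooled couple-level outcomes as primary.
- Include baseline couple HIV status (both negative, discordant, both positive) as a fixed, prespecified covariate in the initiation and adherence models, whatever the baseline comparisons show.
- As prespecified secondary analyses, always report both PrEP initiation and adherence among baseline-negative partners and ART initiation and adherence among baseline-positive partners. Classify by baseline status and describe seroconverters separately.
- State that a pooled effect will not be attributed to either component on the pooled result alone. A rule confining claims to whichever component shows an effect should be avoided, because it invites post hoc selection between the two.

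The cost is wording; status is already collected at screening. Component estimates are less precise: in the split above, 0.47 to 0.61 for couples with an HIV-positive partner and 0.38 to 0.41 for the others, against 0.36 pooled. The both-positive level may be sparse. With assumed prevalences of 20% in one partner and 10% in the other, and independence, it is 0.20 × 0.10 = 2% of couples, about 10 of 480; at 40% and 20% it is 8%, about 38. A rule for merging it with the discordant level should be stated in advance. With a logit link the adjusted odds ratio is conditional on couple HIV status, and the plan should say so.

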### Study aims

This study comprises four specific aims. Aim 1, conducted during the formative phase, was to modify the original CHC intervention to include ART/PrEP with review from our Community Collaborative Board (CCB) and a Peer Advisory Board (PAB). Aim 2 is to evaluate the impact of a stigma awareness and education workshop on community members’ attitudes and behaviors toward young women and men who use AODs and other people seeking HIV services (testing/ART/PrEP) and other health services. Aim 3 is to test the efficacy of the CHC+ to increase both partners’ PrEP/ART initiation and adherence (at 3 and 6 months) and reduce AOD use, sexual risk and GBV, and enhance positive gender norms and communication relative to HTS. Lastly, Aim 4 seeks to examine through mixed methods the interaction of the stigma awareness workshop and the CHC+ on increased PrEP and ART initiation, retention, and adherence among young women and their primary partners (see **Fig 1** for SPIRIT schedule).

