#### Study research design

This study is a four-arm cluster randomized trial that has two interventions: a community stigma awareness workshop (for communities) and the CHC+ (for couples). Specifically, 24 Cape Town communities located near clinics that provide ART and PrEP were randomized into one of four arms (see **Fig 3**): (1) stigma awareness workshop (community) and HTS/PrEP/ART (couples); (2) stigma awareness workshop (community), and HTS/PrEP/ART with the CHC+ (couples); (3) no stigma awareness workshop (community) and HTS/PrEP/ART (couples; control); and (4) no stigma awareness workshop (community), and HTS/PrEP/ART with the CHC+ (couples). Twenty couples (a total of 480 couples), defined as young women and their primary male partners both aged 18 to 30 are recruited from each community. Depending on the study arm of their community, couples are provided with HTS/PrEP/ART and/or the CHC+. Couples are asked to return for two study follow-up appointments at 3- and 6-months post-enrollment. Communities are already assigned to receive either the stigma awareness workshop or no workshop, with baseline and repeated follow-up surveys with community members. Recruitment began in July 5, 2022 and is ongoing.

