#### Randomization

To achieve balance in allocation of population groups across the four study arms, stratified randomization by population group (Black African, Coloured, and Mixed) was conducted. A total of 24 catchment areas were selected from the list of 34 catchment areas. The sampling frame included 8 Black African, 8 Coloured and 8 Mixed communities. Within each of the 3 strata, the 8 areas were randomized to the four study arms in a 2:2:2:2 allocation.

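### The stated contrasts supply neither the workshop-by-CHC+ interaction of Aim 4 nor a pooled CHC+ effect for Aim 3, although the planned model can estimate both

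*Protocol article*

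**What the plan says.** Under Study research design: "This study is a four-arm cluster randomized trial that has two interventions". The four arms it lists form a 2×2 layout:

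| | HTS/PrEP/ART alone | HTS/PrEP/ART with CHC+ |
|---|---|---|
| Workshop | arm 1 | arm 2 |
| No workshop | arm 3 (control) | arm 4 |

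Under Randomization, within each of three strata "the 8 areas were randomized to the four study arms in a 2:2:2:2 allocation", which gives 3 × 2 = 6 communities per arm. Under Sample size: "A sample size of 480 couples, 120 per each of the four study arms".

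Study aims makes Aim 4 a mixed-methods examination of "the interaction of the stigma awareness workshop and the CHC+ on increased PrEP and ART initiation, retention, and adherence". The Abstract and Table 3 repeat this aim.

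Statistical analysis plan and hypotheses describes a logit GEE model with arm, visit and visit-by-arm, the only interaction named. For the hypotheses that CHC+ raises initiation and adherence, it then says: "We will test ART/PrEP initiation and adherence across two arms at a time by estimating contrasts at each time point". No contrast is tied to Aim 4.

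Sample size describes a "nested design model with additivity on the primary intervention effect" and a secondary CHC+ effect, and in the same sentence says "our sample size was selected to ensure power for contrasts based on the presence of an interaction" between workshop and CHC+. It gives minimal effects for the CHC+ arm against the HTS arm, although there are two arms of each kind.

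**The concern.** Three statements do not fit together.

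1. Aim 4 asks whether the effect of CHC+ differs with and without the workshop. That is a difference of two differences, and no comparison of two arms yields it. Followed literally, the stated rule leaves Aim 4 without a quantitative estimate. Finding one simple effect significant and the other not would be no substitute.

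2. Aim 3 asks for the efficacy of CHC+. The analysis section offers only pairs of arms (6 against 6 communities). The sample-size section can be read as pooling over workshop (12 against 12). The choice changes both the estimand and the precision, and the article does not make it.

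3. Additivity means no interaction on the scale of the model. A design sized under additivity gives no assurance about contrasts that matter because an interaction is present. The sentence claims both and identifies no detectable interaction.

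At stake are a named aim without a matching contrast, an ambiguous CHC+ comparison, and the risk that a null Aim 4 result is read as absence of synergy when the trial could see only a very large one.

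**Working it through.** **Inputs from the article (Sample size, Randomization).** 6 communities per arm, 20 couples per community, ICC 0.05, 80% power, two-sided 0.05, follow-up 95% at 3 months and 90% at 6 months.

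**Assumed.** Cohen's h as the effect scale, because the article states none. Normal quantiles: 1.960 + 0.842 = 2.802.

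**The article's own figures first.** Neither the scale nor the control rates are given, so these cannot be pinned down.
- 0.23 (CHC+ against HTS, initiation). As h, the calculation below gives 0.36 pooled and 0.51 for two arms; even with no design effect the pooled value is 0.26. As an absolute difference, it gives about 80% power at 95% follow-up only for a two-arm contrast with an assumed control rate of about 16–20% or 57–61%.
- 0.34 (CHC+ against HTS, adherence at 6 months). This is near the pooled h of 0.37 but does not equal it.
- 0.45 (workshop plus CHC+ against control, initiation). As a two-arm h, it is approached only one-sided (0.454 at 95% follow-up) or with individuals as the unit (0.443 at 95%, 0.447 at 90%).
- 0.26 to 0.6 (effects of the intervention components on adherence). These are not labelled as an interaction.

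No single scale tried reproduces 0.23, 0.34 and 0.45 together, so they do not settle whether pooling was intended.

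**Contrasts.** Let v be the variance of one arm's estimate on the h scale, v = DE / n per arm, with DE = 1 + (m − 1) × ICC.
- One pair of arms, e.g. arm 2 − arm 1: variance 2v.
- Pooled CHC+, ½[(arm 2 − arm 1) + (arm 4 − arm 3)]: variance ¼ × 4v = v.
- Interaction, (arm 2 − arm 1) − (arm 4 − arm 3): variance 4v.

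So one pair has a detectable effect √2 = 1.41 times the pooled one, and the interaction twice the pooled one. These ratios hold at any common ICC.

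**Detectable effect = 2.802 × √(c × v), with c = 1, 2 or 4.**
- 95% follow-up: m = 19, DE = 1 + 18 × 0.05 = 1.90, n = 114, v = 1.90/114 = 0.01667, √v = 0.1291.
- 90% follow-up: m = 18, DE = 1 + 17 × 0.05 = 1.85, n = 108, v = 1.85/108 = 0.01713, √v = 0.1309.

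| Contrast | c | 95% follow-up | 90% follow-up | ICC 0.01–0.10 (assumed), 95% follow-up |
|---|---|---|---|---|
| Pooled CHC+ (12 vs 12) | 1 | 0.36 | 0.37 | 0.29–0.44 |
| One pair (6 vs 6) | 2 | 0.51 | 0.52 | 0.40–0.62 |
| Interaction (all four arms) | 4 | 0.72 | 0.73 | 0.57–0.88 |

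**Power = Φ(h / √(c × v) − 1.96), at 95% follow-up.**
- h = 0.36: pooled Φ(2.79 − 1.96) = 80%; one pair Φ(1.97 − 1.96) = 50%; interaction Φ(1.39 − 1.96) = 29%.
- h = 0.50: pooled 97%, one pair 78%, interaction 49%.

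**Few clusters.** With t quantiles at 95% follow-up, the pooled value becomes 0.38 (22 df) and one pair 0.57 (10 df). With about 20 df the interaction becomes (2.086 + 0.860) × 2 × 0.1291 = 0.76. The ordering does not change.

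**The case against.** A reader might infer that the interaction will never be tested. The article does not support that. Arm as a four-level factor, crossed with visit, is saturated in workshop and CHC+, so the interaction is a linear contrast of coefficients already in the model. Recoding to two factors and their product would give the same fit. The two-arms-at-a-time sentence is tied to the CHC+ hypotheses of Aim 3; the article does not say that Aim 4 will be handled that way. A fuller analysis plan may exist, and Aim 4 is described as mixed methods.

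A reader might also infer that the CHC+ effect uses only half the communities. That is true of each contrast taken alone. Arm 2 against 1 and arm 4 against 3 together use all 24, and the sample-size wording leaves a pooled comparison open.

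Simple effects are a legitimate Aim 3 estimand where an interaction is expected, and the pooled effect is harder to interpret if the interaction is strong. Lastly, 0.72–0.73 is on the arcsine scale, whereas the planned model is a logit model, so it is not the detectable size of a term in that model.

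All of this stands, and it limits the point to the stated contrasts. It does not remove it. The section goes beyond a bare summary: it specifies one interaction and one testing rule, and neither serves Aim 4. If simple effects are intended for Aim 3, the article should say so and size the trial for them. The additivity sentence conflicts with itself whatever a fuller plan contains.

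**Conclusion.** The point holds in limited form. The analysis section states no four-arm contrast for Aim 4, and its rule for pairs of arms does not provide one, although the model can. It names no pooled CHC+ effect, and the sample-size section does not say whether its CHC+ comparison pools over workshop. That section also joins additivity to power in the presence of an interaction.

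The size of the matter follows from the layout: a pair of arms has twice the variance of the pooled CHC+ effect, and the interaction four times. The detectable effects in h are indicative. They rest on the assumed scale and normal quantiles, with the article's ICC and follow-up. On any of the ICCs tried, the sample is weak for the interaction.

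**What to change.** **Analysis section.** Keep the arm-by-visit GEE model.
- Aim 3: name CHC+ against no CHC+, averaged over workshop (12 against 12 communities), as the main contrast. Report both simple effects (arm 2 against 1, arm 4 against 3) beside it.
- Aim 4: add (arm 2 − arm 1) − (arm 4 − arm 3) at each visit where the outcome is assessed, with a 95% confidence interval, reported as estimation.

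**Sample-size section.** Say whether the CHC+ comparison pools over workshop. Resolve the additivity/interaction sentence. Give the scale of every effect size. State that the sample is weak for the interaction, with its detectable size restated by the sponsor on the scale of the planned model; the h values above should not be copied in as they stand.

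**Cost.** Wording only: no change to design, data collection or model. The article describes recruitment as ongoing, so the contrasts should be fixed before outcome data are analysed. The one drawback is that, under a strong interaction, the pooled effect is an average over two workshop conditions. This is why the simple effects must accompany it.
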